### Objectives

The primary objective of the MAMA (Microbiome Changes Due to Antibiotic Prophylaxis in Mothers at Birth) study is to assess the feasibility of a fully remote, nonsite-bound study design for longitudinal gut microbiome research in a peripartum population, including recruitment, sample return, and follow-up completion.

Secondary objectives are to explore compositional changes in the maternal gut microbiome associated with PAP using cefuroxime during CS, compared with vaginal delivery (VD), across the peripartum period.

In this context, the study aims to establish a scalable methodological framework for future remote microbiome studies in maternal health and other vulnerable populations.

## Methods

### Study Design and Setting

The MAMA study was conducted as a prospective, 2-arm observational cohort study comparing women undergoing CS with PAP to women delivering vaginally without intrapartum antibiotic exposure. Recruitment was integrated into routine clinical care, and participants were followed from the third trimester through 90 days postpartum. The study was carried out between May 2022 and March 2024 at 2 German level-1 perinatal centers (Municipal Hospitals of Cologne and St. Marien Hospital Bonn [GFO Kliniken Bonn]) as well as affiliated outpatient providers. An overview of the overall study design and workflow is provided in Figure 1.

**Figure 1. F1:**
[figure not shown]
Study design of the MAMA (Microbiome Changes Due to Antibiotic Prophylaxis in Mothers at Birth) trial: fully remote workflow and sample collection schedule. CS: cesarean section; PAP: perioperative antibiotic prophylaxis; VD: vaginal delivery.

The study was originally conceptualized as a hypothesis-testing cohort design aimed at characterizing maternal gut microbiome trajectories in relation to delivery mode and PAP exposure. However, real-world recruitment constraints in this peripartum population resulted in a smaller and unevenly distributed sample size. In view of these conditions, the present protocol primarily serves as a feasibility investigation of a fully decentralized study framework for maternal microbiome research. Accordingly, subsequent microbiome analyses are defined as exploratory and hypothesis-generating rather than confirmatory.

A contemporaneous comparator group was required to interpret microbial patterns observed after CS. Randomization or withholding of the standard of care was ethically impermissible, and pre-post analyses within CS alone would have conflated antibiotic-associated effects with surgical and physiological consequences of operative delivery. VD therefore represented the most appropriate counterfactual, reflecting postpartum microbial trajectories in the absence of PAP and operative stress. External control datasets were not considered suitable due to widely recognized methodological heterogeneity across microbiome studies (eg, primer regions, sequencing workflows, and bioinformatic pipelines), which limits cross-study comparability.

The study was explicitly implemented as a fully remote, decentralized design to minimize participant burden during pregnancy and early postpartum. All study procedures, including screening, informed consent, questionnaire completion, and stool sampling time points, were completed by participants at home. Communication occurred via telephone or institutional email. Preassembled sampling kits were mailed to participants and included written instructions, a stool catcher, a DNA stabilization tube enabling reliable sample quality even when samples remained at home for several days before mailing, a structured paper–based metadata questionnaire, and a preaddressed return envelope. Participants received reminder notifications from the study coordinator regarding upcoming collection time points and missing documentation. The absence of mandatory on-site visits enabled flexible participation, allowing women to complete all study tasks according to their individual schedules and daily responsibilities. This design facilitated nationwide participation and broadened accessibility, particularly for individuals living in rural areas, with limited mobility, or with substantial childcare and occupational commitments.

The study was developed and implemented in close collaboration between microbiologists, clinical pharmacists, obstetricians, and allied health care professionals, ensuring both methodological rigor and practical feasibility. The reporting of this protocol follows the STROBE (Strengthening the Reporting of Observational Studies in Epidemiology) recommendations (Checklist 1) for observational cohort studies, as recommended by the EQUATOR Network [24].

The study was registered in the German Clinical Trials Register (DRKS00027305), which is part of the WHO International Clinical Trials Registry Platform (ICTRP).

Participants were screened and informed by telephone. Upon inclusion, a postal test kit was sent to eligible participants, which included the written informed consent form, a questionnaire, a feces catcher, a stool collection tube, and a preaddressed return envelope. The signed consent form was returned together with the baseline stool sample (T0). Based on the mode of delivery, participants were assigned to either the CS group with PAP (cefuroxime 1.5 g intravenously) or to the control group with VD (no antibiotic exposure). Follow-up samples were collected at 2 to 3 days postpartum (T1) and 90±10 days postpartum (T2). All procedures were conducted by the participants at home, without the need for on-site visits.

### Ethical Considerations

The study was reviewed and approved by the ethics committee of Witten/Herdecke University (274/2021) in February 2022. A substantial amendment covering the addition of a second study center and modifications to the screening process was approved in September 2022. Recruitment commenced after ethical approval, with the first participant enrolled in May 2022, and the last participant in October 2023. Follow-up concluded in March 2024, with the return of the final stool sample. The remote consent procedure was explicitly reviewed and approved by the ethics committee. All participants provided verbal consent during the initial telephone screening and subsequently returned signed written consent forms together with their first stool sample. Study participation was voluntary, and participants could withdraw at any time without providing reasons. No incentives were provided for participation. All data were collected and processed in pseudonymized form in compliance with the General Data Protection Regulation (GDPR). No directly identifying information was accessible to the research team. The data protection concept was developed in collaboration with the institutional data protection officer and reviewed as part of the ethical application. There was no patient or public involvement in the study design or implementation. Pseudonymized raw data will be made available to qualified researchers upon reasonable request to the principal investigator and in accordance with institutional and GDPR requirements. The study was conducted as part of a doctoral project at the Faculty of Health, Witten/Herdecke University.

### Eligibility and Recruitment

Participants were eligible for inclusion if they were aged at least 18 years, in the third trimester of pregnancy, and planned to deliver either by elective CS or VD without medical indication for peripartum antibiotics. Sufficient German language skills were required to complete the informed consent process and written study documentation. Exclusion criteria comprised participation in another clinical study, chronic inflammatory bowel disease (eg, Crohn disease or ulcerative colitis), hematologic or oncologic disease, chronic renal or hepatic disease, and chronic viral infections such as HIV, hepatitis B virus, or hepatitis C virus. Additional exclusions included systemic use of immunosuppressants, virostatics, cytostatics, proton pump inhibitors, or systemic antimicrobial agents (antibiotics or antifungals) within the past 3 months. Women with a foreseeable need for surgery or antimicrobial treatment other than cefuroxime within the study period (90 days postpartum) were also excluded.

Participants were recruited between May 2022 and October 2023 at 2 German level 1 perinatal centers and affiliated outpatient facilities. Eligible women were identified by attending obstetricians and midwives during routine clinical care. To support recruitment beyond the hospital setting and to address recruiting bias, awareness of the study was raised through posters in clinic waiting areas, printed flyers distributed during antenatal visits, and social media announcements via the official channels of the participating institutions. In addition to reaching a broader population, the social media strategy was specifically intended to include women with low-risk pregnancies who received all prenatal care in the outpatient sector and would otherwise have had limited contact with hospital-based recruitment. This approach aimed to reduce recruitment bias toward high-risk pregnancies, such as those with gestational diabetes, multiple gestation, or prior cesarean delivery. Pregnant women and new mothers represent a population with specific logistical and time-related needs, which informed the choice of a decentralized recruitment and study design.

Interested individuals were first approached by clinical staff and subsequently contacted by the study coordinator. Informed consent was obtained remotely in a 2-step process. Following an initial telephone-based eligibility screening and verbal explanation, participants confirmed their consent in writing by mailing back the signed documents together with their first stool sample and completed questionnaire.

Assignment to study groups was based on the actual mode of delivery. Women initially recruited for the control group who ultimately required CS for medical reasons were reallocated to the intervention group. Recruitment concluded after inclusion of 25 women in the CS group and 12 in the vaginal birth group, without reaching the originally planned sample size.

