### Data Collection and Sample Handling

Sample collection was performed independently by participants at home as part of the fully remote study workflow. Final group assignment (CS vs VD) was based retrospectively on the actual mode of delivery at birth. Each participant was asked to provide 3 stool samples at predefined time points: during late pregnancy (T0, from gestational week 32 onward), within 2 to 3 days postpartum (T1), and at 90 (±10) days postpartum (T2). These time points were selected to capture baseline microbiome composition, immediate peripartum changes, and long-term recolonization dynamics. For each time point, participants received a sample collection kit that included a collection tube (DNA/RNA Shield Fecal Collection Tube, Zymo Research), a single-use stool catcher (Feces Catcher, Zymo Research), written instructions, and a prepaid return envelope. Paper-based questionnaires accompanied each sample kit and covered maternal health status, medication use, pregnancy and birth-related variables, and lifestyle factors such as nutrition and physical activity. Participants returned both the stool sample and completed questionnaire in the same shipment. Questionnaires were designed to be completed within approximately 10 minutes and spanned 2 to 3 pages, depending on the time point. Incomplete or missing forms were actively followed up by the study coordinator.

Samples were shipped by standard postal service and received by the coordinating study center. Although the exact time between sampling and mailing was not recorded for all participants, no sample exceeded the manufacturer’s recommended stability window.

Upon arrival, samples were documented and immediately stored in a temperature-monitored, alarm-secured refrigerator at 4°C to 8 °C, where they remained until DNA extraction. The median storage duration was 434 days (range: 137‐784 d), with no deviations from the defined storage conditions. Despite the stabilizing effect of DNA/RNA Shield, the wide range of storage periods may still cause subtle bias.

The nucleic acid stabilization buffer (DNA/RNA Shield) ensures preservation of microbial DNA for at least 24 months at ambient temperature (4° C‐25  °C) and indefinite stability when frozen (<−20 °C), according to the manufacturer. Accordingly, all returned samples were accepted for processing. No exclusions were made due to transport delays, damage, or temperature fluctuations.

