Missing data will not be imputed. Samples with insufficient sequencing depth will be excluded from diversity analyses but may be retained for descriptive taxonomic summaries. Sensitivity analyses will be considered to evaluate the robustness of key findings. Sensitivity analyses may include rerunning key comparisons with alternative distance metrics or differential-abundance methods. If imbalances in relevant maternal variables (eg, prevalence of gestational diabetes) are observed between study groups, multivariate statistical models (eg, generalized linear models and redundancy analysis) will be applied to adjust for potential confounding effects. Stratified analyses or subgroup comparisons may also be conducted if sample size permits.

All statistical analyses will be performed in Python, using QIIME 2-compatible plugins (eg, ANCOM-II) and standard scientific Python libraries. Software versions and analysis scripts will be documented for reproducibility.

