## Results

The recruitment and sample collection phase of the study has been completed. Between May 2022 and October 2023, a total of 37 participants were enrolled, including 25 women in the CS group and 12 in the VD group. Recruitment concluded below the originally planned sample size, reflecting real-world constraints in this peripartum population. Follow-up was completed with receipt of the final stool sample in March 2024. An overview of baseline characteristics of participants who returned at least one stool sample is presented in Table 1. DNA extraction and 16S rRNA gene sequencing were completed in a single batch in October 2024. All samples passed quality control and were retained for downstream analyses. An overview of included and excluded samples by group and time point is provided in Figure 2. Bioinformatic processing and statistical analyses were initiated in June 2025 and were ongoing as of December 2025.

**Table 1. T1:** Baseline characteristics of participants who submitted at least 1 sample (N=31)^a^.

Characteristic		Total (N=31)	CS^b^ with PAP^c^ (n=20)		VD^d^ without PAP (n=11)	
Continuous variables						
Age (y), median (IQR)		37 (33-39)	37 (33-39)		36 (33-38)	
Categorical variables, n (**%**)						
Delivery mode						
CS		20 (65)	20 (100)		—^e^	
VD		11 (35)	—		11 (100)	
Multiple births						
Yes		2 (6)	2 (10)		0 (0)	
No		29 (94)	18 (90)		11 (100)	
Parity						
0		12 (39)	9 (45)		3 (27)	
1		13 (42)	5 (25)		8 (73)	
2		5 (16)	5 (25)		0 (0)	
3		0 (0)	0 (0)		0 (0)	
4		0 (0)	0 (0)		0 (0)	
5		1 (3)	1 (5)		0 (0)	
>1		19 (61)	11 (55)		8 (73)	

a Only participants in the CS group received PAP; no antibiotics were administered in the VD group.

b CS: cesarean section.

c PAP: perioperative antibiotic prophylaxis.

d VD: vaginal delivery.

e Not applicable.

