**Figure 2. F2:**
[figure not shown]
Flowchart of participant enrollment, allocation, follow-up, and analysis in the MAMA (Microbiome Changes Due to Antibiotic Prophylaxis in Mothers at Birth) study, in line with the STROBE (Strengthening the Reporting of Observational Studies in Epidemiology) recommendations for observational studies. CS: cesarean section; VD: vaginal delivery.

A per-protocol sample was defined as a stool sample received within the prespecified time window and passing quality control. Protocol deviation was defined as exclusion from the per protocol set due to intake of antimicrobial agents (antibiotic or antifungal) other than the study medication or as sample collection outside the defined protocol windows and could not be assigned to a valid time point. Two women, who were initially allocated to the vaginal delivery group, delivered by CS and were therefore analyzed in the CS group; these women are counted under vaginal delivery at baseline (T0) and under CS at follow-up (T1 and T2). Numbers reported per group reflect participants analyzed at each time point; totals across groups were: T0 (n=31), T1 (n=19), T2 (n=21), and final analysis (N=71).

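### Parity of 2 or more and multiple births occur only in the CS group, which also mixes planned and unplanned CS: full-group adjustment has no VD information there, so a comparison restricted to the overlap is needed

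*Protocol article*

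**What the plan says.** Under Eligibility and Recruitment, women could enter if they "planned to deliver either by elective CS or VD without medical indication for peripartum antibiotics". Entry is therefore by intention. Grouping is by what happened: "Final group assignment (CS vs VD) was based retrospectively on the actual mode of delivery at birth" (Data Collection and Sample Handling). The same recruitment section adds that "Women initially recruited for the control group who ultimately required CS for medical reasons were reallocated to the intervention group". The note to Figure 2 gives the number: "Two women, who were initially allocated to the vaginal delivery group, delivered by CS and were therefore analyzed in the CS group". It also says that these two are counted with the VD group at T0 and with the CS group at T1 and T2.

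Eligibility sets no limit on parity or multiple gestation. The recruitment text nevertheless names multiple gestation and previous cesarean among the high-risk features toward which recruitment might be biased.

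Table 1 in Results ("Baseline characteristics of participants who submitted at least 1 sample (N=31") describes 20 CS and 11 VD women.

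If relevant maternal variables turn out to be imbalanced, the Statistical Analysis Plan section says that "multivariate statistical models (eg, generalized linear models and redundancy analysis) will be applied to adjust for potential confounding effects". Stratified or subgroup analyses are optional and depend on numbers. No comparison restricted to women who have a counterpart in the other group is specified.

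**The concern.** Model adjustment borrows information from women in both groups who share a covariate value. Where one group has nobody at that value, the data cannot show how a VD woman of that kind would have looked. The model then relies on its functional form, or those women stop contributing to the group contrast. The article names parity as a variable for adjusted or stratified analysis in several places. An adjusted CS-VD result could therefore be read as having dealt with parity when, for parity 2 or more, the data hold no VD information.

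Unplanned CS raises a separate issue. It may follow labour and has a medical indication, so the CS group is a mixed exposure rather than the single one that the entry criterion suggests. The findings are meant to inform the design of later studies, so both points matter even in an exploratory analysis.

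**Working it through.** **1. Counts from Table 1.**

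| | CS | VD |
|---|---|---|
| Parity 0 | 9 | 3 |
| Parity 1 | 5 | 8 |
| Parity 2 | 5 | 0 |
| Parity 5 | 1 | 0 |
| Sum | 20 | 11 |
| Multiple births | 2 | 0 |

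The rows add up to the column totals and the printed percentages reproduce. Parity 2 or more is 5 + 1 = 6/20 (30%) for CS and 0/11 for VD. Multiple births are 2/20 (10%) and 0/11.

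**2. The summary row.** Table 1 also has a row labelled >1 with 19 in total, 11 CS and 8 VD. From the single-value rows, parity above 1 is 6, 6 and 0. Parity of 1 or more is 13 + 5 + 1 = 19 in total, 5 + 5 + 1 = 11 CS and 8 VD. The row is therefore parity 1 or more under a wrong label. As printed, it makes the VD group look more parous (73% against 55%) and hides the gap of 6 against 0.

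**3. Size of the overlap.** Table 1 does not cross-tabulate, so only bounds are possible.
- CS women with parity 2 or more, a multiple birth or an unplanned CS: at least max(6, 2, 2) = 6, at most 6 + 2 + 2 = 10.
- CS women remaining: 20 − 10 = 10 to 20 − 6 = 14.
- VD women remaining: all 11.

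**4. Effect of the planned adjustment.** As an illustration, take an outcome equal to 1 at parity 2 or more and 0 otherwise, with no true group effect.
- Unadjusted: 6/20 − 0/11 = 0.30.
- Linear parity: mean parity is 20/20 = 1 (CS) and 8/11 = 0.727 (VD). The within-group sum of squares is (50 − 20) + (8 − 64/11) = 32.18. The cross-product is 15 − 20 × 1 × 0.30 = 9 for CS and 0 for VD. The slope is 9/32.18 = 0.280. The adjusted difference is 0.30 − 0.280 × (1 − 0.727) = 0.22.
- Indicator for parity 1 or more: the proportions are 0.55 and 0.727. The sum of squares is 20 × 0.55 × 0.45 + 11 × (8/11) × (3/11) = 7.13. The cross-product is 6 − 20 × 0.55 × 0.30 = 2.7. The slope is 2.7/7.13 = 0.379. The adjusted difference is 0.30 − 0.379 × (0.55 − 0.727) = 0.37.
- Separate indicator for parity 2 or more: it fits the outcome exactly, so the group coefficient is 0.

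A simulated outcome was also run on the Table 1 parity layout, with assumed positions for the multiple births and unplanned CS. One indicator per unsupported cell gave a group coefficient of 0.123, the same as dropping those women (0.123). Additive indicators gave 0.087. The coding decides whether the model extrapolates or becomes the restricted analysis.

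**5. Attrition.** The Figure 2 note gives 31, 19 and 21 samples at T0, T1 and T2. The text shown here has no split for the overlap set. If losses were proportional (an assumption), the set would hold about 10 × 19/31 = 6 to 14 × 19/31 = 9 CS against 11 × 19/31 = 7 VD at T1. At T2 it would hold about 7 to 9 CS against 7 VD (10, 14 and 11 times 21/31).

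**The case against.** The strongest reply is that the plan permits a model that does the right thing. Neither covariate is collinear with group, since 14 CS women have parity 0-1 and 18 are singletons. One indicator per unsupported cell gives exactly the restricted contrast, and covariate coding is commonly left to a fuller analysis plan. This is correct. A reader might infer that regression cannot adjust here at all, or that the terms would drop out; the counts do not support that. What stands is that such a model answers the question only for the overlapping women, and the article does not say so.

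Second, a reader might take the two unplanned CS as an eligibility breach. They are not: both women planned VD, and the switch to actual mode is stated openly. An unplanned CS can have no VD counterpart by definition, so this is a mixed exposure rather than a failure of covariate overlap.

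Third, the empty VD cells may be chance. Fisher's exact two-sided p is 0.066 for parity 2 or more and 0.53 for multiple births, and 0/11 has a one-sided 95% upper bound of 1 − 0.05^(1/11) = 24%. This argues against exclusion by design. It does not put VD women into these strata.

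Fourth, within-woman comparisons over time are planned, and parity and multiplicity are fixed within a woman. They can bias those contrasts only by altering the change over time. This narrows the concern but leaves the group comparisons at each time point.

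Finally, Outcomes, Discussion and Limitations already concede residual confounding and weak multivariable analysis, and the microbiome analyses are declared exploratory. That lowers the stakes. A general caveat does not tell the reader which strata lack a comparator.

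**Conclusion.** The point holds in a limited form. Six of 20 CS women (parity 2 or more) and two of 20 (multiple births) have no VD counterpart in Table 1, and the CS group includes two unplanned CS. Adjustment across the full 20 against 11 has no VD information in the parity and multiplicity strata. Depending on coding, it extrapolates or reduces to the overlap. The values 0.22 and 0.37 come from an invented outcome and show the mechanism, not an expected bias in this study.

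It would go too far to say that the groups cannot be compared: 10 to 14 CS women do overlap with the 11 VD women on these factors. That range assumes that both unplanned CS are among the 20 in Table 1, which fits a VD column made up wholly of vaginal births. It covers the 31 women with at least one sample, not all 37 enrolled, and precedes the fall to 19 and 21 samples.

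Counting two women under VD at T0 and under CS later also conflicts with grouping by actual mode of delivery and must be reconciled.

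**What to change.** - Beside the main CS-VD results, report one sensitivity comparison: planned elective CS, singleton, parity 0-1, against VD.
- Label it as chosen after Table 1 was seen; analyses have been under way since June 2025, so it cannot be called pre-specified.
- Give the number of overlapping women in each group at T0, T1 and T2.
- Do not describe model-adjusted results as having controlled for parity 2 or more or multiple gestation.
- Describe the CS group as mixed planned and unplanned CS.
- Reconcile the T0 counting in the Figure 2 note with the grouping rule in Eligibility and Recruitment and in Data Collection and Sample Handling, and apply one rule at all time points.
- Correct the label of the >1 parity row.

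Agreement in direction between the full and restricted sets should not be a condition for drawing conclusions, because one set is nested in the other.

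The cost is one extra analysis of data already collected. The restricted set will be imprecise, especially at T1 and T2, and its results remain exploratory.
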